### Primary outcome

The primary outcomes of our study are the changes in the Western Ontario and McMaster Universities Osteoarthritis Index (WOMAC) subscales for pain, stiffness, and physical function. These subscales are assessed at baseline and followed up at 12, 24, and 48 weeks post-intervention. The WOMAC is a widely recognized tool for evaluating knee and hip osteoarthritis, consisting of 24 items distributed across the three subscales (38). The pain subscale includes five questions scored from 0 to 10, summing up to a total of 0–50 points. The stiffness subscale comprises two questions, also scored from 0 to 10, with a total score range of 0–20. The physical function subscale contains seventeen questions, each scored from 0 to 10, resulting in a total score from 0 to 170. The total WOMAC score ranges from 0 to 240, with higher scores reflecting more severe disease. This comprehensive evaluation will allow us to assess the immediate and long-term effects of the interventions on the symptoms and functional limitations associated with knee osteoarthritis.

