**Figure 1 F1:**
[figure not shown]
Study flow diagram.

The primary outcomes encompass the pain, stiffness, and physical function subscales of the Western Ontario and McMaster Universities Arthritis Index (WOMAC) (27). Secondary outcomes will be assessed using the Berg Balance Scale, which evaluates balance performance through a series of functional tasks; the 6-minute walk test, which measures endurance and mobility by assessing the distance walked in 6 min; and the Health Survey Short Form (SF-36), a comprehensive questionnaire that assesses overall health-related quality of life across multiple domains. These measures will provide a holistic view of the participants' physical and psychosocial well-being. Outcome measurements will be conducted at baseline, immediately following the 12-week intervention period, and at 24 and 48 weeks to assess the durability of treatment effects. The personnel administering the physical function evaluations and the data analyst are unaware of the participants' treatment allocations. The specific endpoints and their categorization as outcomes are detailed in Table 1.

**Table 1 T1:** Schedule of assessments for primary and secondary outcomes.

Time	Baseline	Week 12	Week 24	Week 48
Primary Outcome variables				
WOMAC^a^—Pain	×	×	×	×
WOMAC—Physical Function	×	×	×	×
WOMAC—Stiffness	×	×	×	×
Secondary outcome variables				
SF-36^b^	×	×	×	×
Berg Balance Scale^c^	×	×	×	×
6 min walk test^d^	×	×	×	×

a WOMAC: Western Ontario and McMaster Universities Osteoarthritis Index.

b SF-36: Medical outcome survey short-form 36.

c Berg Balance Scale: A 14-item test that measures a person's balance and walking abilities.

d 6 min walk test: A simple test that measures how far a person can walk in six minutes.

The study setting is the Zhongshan Hospital of Traditional Chinese Medicine, affiliated with Guangzhou University of Traditional Chinese Medicine, located in Zhongshan, Guangdong, China. The study received ethics approval from the Institutional Review Board of Zhongshan Hospital of Traditional Chinese Medicine.

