### Study intervention

The study interventions are designed to compare the clinical effectiveness of Tai Chi, Baduanjin, and a health-education program in older adults with knee osteoarthritis. The interventions will be conducted concurrently to avoid seasonal influences on disease severity. The primary goal is to assess the impact of these interventions on pain, stiffness, physical function, and overall quality of life over a 48-week period.

During the initial 12-week period, participants in the Tai Chi and Baduanjin groups will receive supervised group training sessions, while those in the health-education group will attend weekly sessions focused on educational content related to knee osteoarthritis management. After the 12-week intervention period, participants in all groups will be followed up at Weeks 24 and 48 to evaluate the long-term effects of the interventions. There will be no additional structured intervention programs during the follow-up period; however, participants will be encouraged to continue practicing the exercises they learned during the initial 12 weeks on their own.

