## Statistical analysis

All statistical analyses will be performed using SPSS Statistics version 26.0 (IBM Corp). Continuous variables will be first assessed for normality using the Shapiro–Wilk test and for homogeneity of variance using Levene's test. Data presenting a normal distribution will be expressed as mean ± standard deviation (SD). For comparisons among the three groups, one-way Analysis of Variance (ANOVA) will be used. If the ANOVA indicates a significant difference, *post-hoc* pairwise comparisons will be conducted using the Bonferroni correction to adjust for multiple testing. Non-normally distributed variables will be presented as median (interquartile range, IQR) and analyzed using the Kruskal–Wallis H test, followed by Dunn's test with Bonferroni correction for pairwise comparisons if significant. Categorical variables will be expressed as frequencies (percentages) and compared using the Chi-square test or Fisher's exact test where expected cell counts are less than 5.

For the primary outcome (change in clinical scores from baseline to post-intervention), repeated measures ANOVA will be employed, with Group as the between-subject factor and Time as the within-subject factor. If a significant interaction effect (Group × Time) is observed, simple main effects will be analyzed to determine differences between specific groups at each time point, with Bonferroni adjustments applied for multiple comparisons. A two-sided *p*-value < 0.05 will be considered statistically significant.

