### Analysis

The primary outcomes for this study are defined as the changes from baseline to Week 12 in the three WOMAC subscales: Pain, Stiffness, and Physical Function. The primary analysis will be conducted using an intention-to-treat approach, where all participants are analyzed in the group to which they were randomized, without adjustment for covariates, and with missing 12-week outcomes imputed as no change. Secondary analyses will adjust for baseline characteristics that differ significantly by treatment group, including gender, initial pain severity, medication use, disease duration, and the number of chronic conditions.

Changes in knee pain at weeks 24 and 48, along with all other outcomes, are considered secondary and will be analyzed in the same manner as the primary outcome. We will also perform a longitudinal analysis across all four time points to identify potential time trends and interactions between treatment effects and time. These analyses will utilize mixed-effects models with random intercepts for participants and fixed effects for time, considering autoregressive structures for residual errors.

To handle missing values, we will employ multiple imputation techniques under the assumption of missing at random (MAR). Given the potential for early dropout due to poor outcomes, we will also explore models that account for missing not at random (MNAR) based on informative dropout assumptions. As part of our sensitivity analyses for missing data, we will consider Bayesian models that can incorporate prior assumptions about the non-ignorable missing data mechanisms.

All statistical tests will be two-tailed, with a significance level set at *p* < 0.05. We will conduct both individual time-point analyses and longitudinal analyses to provide a comprehensive understanding of the treatment effects over time.

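### The primary time point is not stated consistently: two sections fix WOMAC at week 12, while Primary outcome, Table 1 and Statistical analysis leave weeks 24 and 48 inside the primary outcome

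*Protocol article*

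**What the plan says.** Two sections of the protocol article fix week 12.

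- **Analysis**: "The primary outcomes for this study are defined as the changes from baseline to Week 12 in the three WOMAC subscales". It continues: "Changes in knee pain at weeks 24 and 48, along with all other outcomes, are considered secondary".
- **Sample size**: the calculation is for the WOMAC change at week 12, adjusted for baseline.

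Other places do not separate week 12 from the later visits.

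- **Primary outcome**: the outcomes are changes in the three subscales, with no visit named as decisive. The section says "These subscales are assessed at baseline and followed up at 12, 24, and 48 weeks post-intervention" and that the evaluation will "allow us to assess the immediate and long-term effects of the interventions on the symptoms and functional limitations".
- **Study design overview**: "The specific endpoints and their categorization as outcomes are detailed in Table 1". In Table 1 the three WOMAC subscales stand in the primary block, marked at baseline and weeks 12, 24 and 48.
- **Statistical analysis**: "For the primary outcome (change in clinical scores from baseline to post-intervention), repeated measures ANOVA will be employed". If the Group × Time interaction is significant, groups are compared at each time point.
- **Study intervention**: "The primary goal is to assess the impact of these interventions on pain, stiffness, physical function, and overall quality of life over a 48-week period".

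**The concern.** A reader who looks up the primary outcome in the section of that name, or in the table said to classify the endpoints, does not find week 12 singled out. A reader of the Analysis section does. Durability to 48 weeks is a headline aim in the abstract, so the later visits will carry weight in the report.

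Suppose the WOMAC comparison is null at week 12 and significant at week 48. Under Analysis this is a secondary signal beside a null primary outcome. Under Primary outcome, Table 1 and the repeated-measures paragraph it could be presented as a primary result. As the text stands, that choice could be made after the data are seen.

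**Working it through.** **1. The passages side by side**

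| Section | Time point for primary WOMAC | Weeks 24 and 48 |
|---|---|---|
| Analysis | Week 12, explicit | Secondary, explicit |
| Sample size | Week 12 | Not used |
| Primary outcome | None named | Listed as follow-up; long-term effects included in the purpose |
| Table 1 | None singled out | Marked in the primary block |
| Statistical analysis | Baseline to post-intervention | Groups compared at each time point |
| Study intervention | 48-week goal | Included |

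The Statistical analysis row is mixed. Its parenthesis fits week 12, because Measurements places the assessment immediately after the intervention at 12 weeks. Its model and follow-up tests run over time points.

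**2. What the sample size supports**

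Inputs from Sample size: three groups, f = 0.32, two-sided α = 0.05, power 0.80, dropout 15%. With one covariate, the noncentral F has 2 and N − 4 degrees of freedom and noncentrality N·f².

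- The smallest N with power 0.80 is 98, or 99 for equal groups.
- With dropout: 98/0.85 = 115.3, so 116; 99/0.85 = 116.5, so 117. The plan states 120, so its figure is reproduced within 3%.
- At 120 × 0.85 = 102 evaluable, power is 0.82.

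This is one test at one visit. On the same inputs with Bonferroni, power at 102 evaluable is 0.68 for three tests (α = 0.05/3 = 0.0167) and 0.53 for nine (α = 0.05/9 = 0.0056). The stated N therefore supports a single week-12 test and was not built for a primary outcome spread over visits.

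**3. What the label is worth in false-positive terms**

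Assumption: one three-group overall test per subscale and visit, each at 0.05 without adjustment. Week 12 only gives 3 × 1 = 3 primary tests; weeks 12, 24 and 48 give 3 × 3 = 9.

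For independent tests the chance of at least one false positive is 1 − 0.95^m:

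- m = 3: 14.3%
- m = 9: 37.0%

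For correlated tests the figures are simulated, with equal correlation ρ and a 2-df chi-square approximation to the F test. The documents give no ρ.

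| ρ (assumed) | 3 tests | 9 tests | Ratio |
|---|---|---|---|
| 0 | 14.3% | 37.0% | 2.6 |
| 0.5 | 12.7% | 27.5% | 2.2 |
| 0.7 | 11.2% | 20.8% | 1.9 |
| 0.8 | 9.9% | 17.1% | 1.7 |

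A separate simulation with F tests and 40 per arm agrees within half a percentage point at ρ = 0.5 to 0.8 (nine tests: 27.8%, 20.4%, 16.8%; three tests: 12.6%, 11.5%, 10.1%).

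**4. The count under the repeated-measures model**

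That model gives one Group × Time test per subscale, so three tests whichever visits enter it. The nine-test figures do not describe that route.

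**The case against.** The strongest reply is that the time point is fixed. Analysis defines it in terms and demotes the later visits; Sample size agrees. Table 1 is captioned "Schedule of assessments for primary and secondary outcomes" and marks baseline in the same way as the other visits. Since baseline cannot be a change endpoint, the marks show visits, and the categorisation may mean only the row blocks. The Primary outcome sentence says when subscales are measured, not which visit decides. The 48-week goal in Study intervention also names quality of life, which is secondary elsewhere, so it reads as a general aim.

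Much of this stands. A reader might infer that the documents declare the week-24 and week-48 changes primary; no sentence does. A reader might also infer nine primary tests with no multiplicity control at all. The repeated-measures route gives three interaction tests, and its time-point comparisons follow only a significant interaction, with Bonferroni adjustment. The count of nine draws on Analysis instead, which analyses other time points in the same manner as the primary and states no adjustment across subscales or visits. Nor is the error rate always more than doubled: at assumed correlations of 0.7 to 0.8 the ratio is about 1.7 to 1.9. Finally, a reader might infer that the choice decides whether the trial is positive. The article gives no rule on whether any or all subscales must succeed, so that is not settled even with week 12 fixed.

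What the reply does not remove is that the section headed Primary outcome omits the visit, the table named as the source of categorisation does not separate the visits, and the model for the primary outcome compares groups at each of them. This is a mismatch within the text, not a detail left to an analysis plan.

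**Conclusion.** The concern holds as an inconsistency in the primary time point. Week 12 is the best-supported reading, but the text leaves room to report a WOMAC result at week 24 or 48 alone as primary.

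On the assumption of separate unadjusted tests per subscale and visit, admitting the later visits moves the chance of at least one false-positive primary test from about 10–14% to about 17–37%, for assumed correlations from 0.8 down to 0. The range rests on that testing scheme and on correlations the documents do not give. The inconsistency itself rests on neither. The point should be corrected, mainly because it concerns which result may be called primary once the data are known.

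**What to change.** Make week 12 the only primary time point, as Analysis and Sample size already do.

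- **Primary outcome**: define the outcomes as the subscale changes from baseline to week 12, with the later visits as secondary.
- **Table 1**: mark or footnote WOMAC at week 12 as primary and at weeks 24 and 48 as secondary.
- **Statistical analysis**: state that the primary comparison is the week-12 group difference, and that the Group × Time test and later time-point comparisons are secondary. Without this change the ambiguity survives the other edits.
- **Study intervention**: describe 48-week effects as a secondary objective.

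The cost is wording in three sections and one table. Study status and timeline says that recruitment had not begun and no data had been analysed at submission, so the change can be made without knowledge of results. The downside is that a week-24 or week-48 result can no longer be reported as a primary finding.

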### Secondary outcomes

The secondary outcome measures in our study comprise the Health Survey Short Form (SF-36) (39), the Berg Balance Scale (40, 41), and the 6 min walk test (42, 43). These assessments aim to provide a detailed evaluation of various aspects of health and function related to knee osteoarthritis. The SF-36 is utilized to assess health-related quality of life across multiple dimensions, offering a broad perspective on the participants' general health status. The Berg Balance Scale evaluates balance and walking abilities, which are crucial for determining functional independence and fall risk in older adults. The 6-minute walk test measures endurance and mobility, providing insights into the participants' physical capacity and activity levels. Detailed descriptions of these measures and their specific application within our study are provided in the following sections.

The 36-Item Short Form Health Survey (SF-36) is a multidimensional health measurement instrument comprising nine scales and 36 items, designed to assess eight health domains: Physical Functioning (PF), Role Physical (RP), Bodily Pain (BP), General Health (GH), Vitality (VT), Social Functioning (SF), Role Emotional (RE), and Mental Health (MH). Additionally, there is a single item assessing Health Transitions (HT), which reflects perceived changes in health status compared to one year prior; this item is not included in the scoring of the subscales or the overall summary measures, but rather provides insight into the dynamic changes over time.

The SF-36 can be self-administered, administered by a trained interviewer, or completed via telephone. The typical completion time ranges from 5 to 10 min, although it may take up to 15 min for elderly participants. Scoring involves a weighted sum of item scores within each subscale to produce a raw score, which is then transformed into a standard score ranging from 0 to 100. Higher scores on the SF-36 indicate better health-related quality of life.

The Berg Balance Scale (BBS) is a widely utilized, reliable, and valid instrument designed to assess balance and functional mobility in individuals with various health conditions, including those with musculoskeletal disorders, neurological impairments, and the elderly. Comprising 14 items, the BBS evaluates a range of activities from sitting to standing, transferring, and walking, each scored on a 0–4 scale, where 0 indicates the inability to perform the task and 4 signifies the ability to perform the task independently without any assistance. The total score ranges from 0 to 56, with higher scores reflecting better balance and functional mobility.

The Berg Balance Scale (BBS) is an especially pertinent tool in the context of osteoarthritis, significantly aiding in the identification of patients at heightened risk for falls and monitoring advancements in balance-oriented rehabilitation programs. This scale is not only efficient to administer, typically taking 20–30 min, but also versatile, making it appropriate for diverse settings such as clinical assessments, rehabilitation facilities, and even home-based evaluations. Its responsiveness to change is particularly advantageous for appraising the impact of therapeutic interventions that target balance enhancement and fall risk mitigation in individuals with osteoarthritis. By providing a sensitive measure of balance and functional mobility, the BBS plays a crucial role in the comprehensive management of patients with this chronic condition.

The 6 min walk test (6MWT) is a straightforward yet robust assessment tool for evaluating an individual's functional exercise capacity and endurance. It entails having participants walk as far as possible along a flat, straight course within a six-minute timeframe. This test is especially valuable for assessing patients with conditions that impair mobility, such as osteoarthritis, heart failure, and pulmonary diseases. Conducted in a controlled environment with minimal distractions, the 6MWT is a safe, low-cost procedure that seamlessly integrates into clinical settings, rehabilitation programs, and research. It measures the distance walked, which corresponds to the patient's exercise capacity and provides insights into their ability to perform daily activities. The test is well-tolerated and offers a practical means of gauging a patient's physical capabilities.

Moreover, the 6MWT is sensitive to changes over time, rendering it an excellent tool for monitoring the effectiveness of interventions like physical therapy, medication, and lifestyle changes. Its reliability and validity have been established across diverse patient populations, including those with osteoarthritis. The 6MWT helps in assessing how disease and treatment influence physical function and overall quality of life, making it an indispensable part of comprehensive patient care and outcome evaluation.

### Adherence

Ensuring participant adherence to the study interventions is critical for the validity of our findings. To enhance compliance, we will implement a multifaceted strategy. For the Tai Chi and Baduanjin groups, attendance will be meticulously tracked during the initial 12-week supervised sessions, with personalized feedback from instructors to boost engagement. Home practice will be encouraged, monitored via weekly feedback forms, and reinforced with monthly follow-up calls post the intervention period. The health-education group will engage in weekly interactive sessions to sustain interest. All participants will receive regular adherence reminders and incentives at key study milestones to acknowledge their contributions.

Post-intervention, adherence will be assessed through monthly phone calls using standardized questionnaires, focusing on the frequency and duration of exercises. This approach will provide a comprehensive view of long-term engagement with the interventions, crucial for evaluating the sustainability of the study effects.

### Safety

Throughout the study, participant safety is of paramount importance. We will conduct weekly assessments during the intervention phase to identify any adverse events, which are defined as any unfavorable or unintended signs, symptoms, or medical conditions. Each adverse event will be meticulously documented on a standardized case report form and subsequently evaluated by the study's rheumatologist. This evaluation will determine the relevance of the event to the intervention and its severity, adhering to the criteria mandated by the Institutional Review Board (IRB).

The recorded adverse events will be categorized and analyzed for any patterns that may suggest potential safety risks to participants. Special attention will be given to serious adverse events and those considered related to the study interventions. Safety monitoring will be conducted throughout the entire study duration, from baseline through the final follow-up at week 48. While intensive monitoring occurs during the 12-week intervention phase, systematic surveillance for adverse events (AEs) will continue during the post-intervention follow-up periods (weeks 24 and 48).

This safety monitoring plan has been reviewed and approved by the ethics review board and an independent data and safety monitoring board, ensuring that the study adheres to the highest standards of participant safety and ethical conduct.

### Data management

In our study, data will be systematically collected and managed through the hospital's internal clinical information system (CIS), which is designed to handle sensitive medical data with high security standards. For participants who are unable to directly input their data into the CIS, paper-based case report forms will be utilized. These forms will be completed by the participants and subsequently entered into the CIS by trained study staff members. The entered data will be verified for accuracy and completeness before being stored securely in the participants' electronic files, which will be kept in a restricted access area within the hospital's information system.

To ensure data integrity and confidentiality, no personal identifiers will be included in the study database. Data will be extracted from the CIS and transferred into statistical software for analysis, ensuring that the process adheres to strict privacy protocols. The CIS also features an audit trail function that logs every instance of data modification, whether by participants or staff, providing a transparent record of all changes made to the data entered into the system.

This approach to data management not only ensures the security and confidentiality of participant information but also facilitates efficient data processing and analysis, which are essential for the reliability and validity of our study outcomes.

